#### Power

Sample size calculation was based on the primary outcomes of the study: at least 50% reduction in expired-air CO readings from the baseline numeric CO readings. Because the Original variety is included in the complete flavors, we do not expect the occurrence of the main outcome to be lower in the complete flavor arms compared to the Original arms, so we will use 1-sided tests with an α level of 0.05 and power of 0.80. Sample size calculation was conducted using Stata 16 (StataCorp).

For objective 1, we assumed an incidence of at least 50% reduction in CO readings of 60% in Group I and 45% in the Original arm at week 3, and incidence of the main outcome among 80% in Group I and 60% in Group IIa at week 6. Based on these values, it was estimated that 136 participants and 64 participants per arm will be needed, respectively. Numeric CO readings will be analyzed as a continuous variable, which typically has higher levels of statistical power [26]. Assuming a mean CO of 6 ppm in Group I and SD of 5 [27], a sample size of 136 per arm will be able to detect a difference of 1.7 between study groups.

For objective 2, we assumed an incidence of at least 50% reduction in CO readings for 70% of those in Group IIb and 45% among the Group IIa at week 6 among the nonresponders in Group II (ie, those who did not reduce cigarette consumption by ≥50% at week 3). Based on these values, we estimated that 48 participants per group will be needed. Assuming 55% of participants in Group II will be nonresponders at week 3; we estimated that a total of 175 participants will be needed in Group II at baseline.

For objective 3, we assumed that 85% in Group IIb and 60% in Group IIa will maintain their responder status at week 6 among responders in Group II (ie, those who reduce cigarette consumption by ≥50% at week 3). Based on these values, it was estimated that 39 participants per group will be needed. Assuming 45% of participants in Group II will be responders at week 3, a total of 174 participants will be needed in Group II at baseline.

Based on these calculations, we will randomly assign 150 participants to Group I and 250 participants to Group II at baseline.

Objective 4 is considered exploratory in nature. Given the above sample size, 125 participants per group will be able to detect a difference between 80% and 67% of at least 50% of CO reduction comparing immediate versus delayed access to complete flavor profile.

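### The week-6 planning rates for Group IIa do not fit together (strata average 51.75%, Objective 1 uses 60%), Objective 3's endpoint is unclear, and Objective 4's detectable difference falls short of 80% power

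*Protocol article*

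**What the plan says.** All figures are in the Protocol article, Methods, Analytic Plan, Power. Objectives are numbered here as in that section: 2 concerns week-3 nonresponders and 3 concerns week-3 responders.

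- Endpoint: "Sample size calculation was based on the primary outcomes of the study: at least 50% reduction in expired-air CO readings".
- Test: "so we will use 1-sided tests with an α level of 0.05 and power of 0.80".
- Objective 1, week 6: "80% in Group I and 60% in Group IIa at week 6". With the week-3 rates ("60% in Group I and 45% in the Original arm at week 3") this leads to the statement that "it was estimated that 136 participants and 64 participants per arm will be needed, respectively".
- Objective 2: "70% of those in Group IIb and 45% among the Group IIa at week 6 among the nonresponders in Group II", 48 per group, with 55% of Group II taken to be nonresponders.
- Objective 3: "85% in Group IIb and 60% in Group IIa will maintain their responder status at week 6", 39 per group, with 45% of Group II taken to be responders.
- Objective 4, labelled exploratory: "125 participants per group will be able to detect a difference between 80% and 67" (percent).

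Allocation is 150 to Group I and 125 each to Groups IIa and IIb (Randomization). The Outcome Measures section defines a responder by self-reported cigarette consumption, not by CO.

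**The concern.** Nonresponders and responders together make up the whole of Group IIa, so its overall week-6 rate must be the weighted average of the two stratum rates. With strata at 45% and 60%, the average can reach 60% only if everyone is a responder, and the section itself puts responders at 45%. Either the rate used for Objective 1 or at least one stratum rate is then wrong, unless the Objective 3 rates belong to a different outcome.

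At stake is whether the stated sample sizes rest on one consistent picture of week 6, and whether a reader can tell which endpoint Objective 3 was sized on. The same stratum rates also imply a week-6 rate for Group IIb. That rate bears on how informative the comparison of immediate with delayed access (Objective 4) can be.

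**Working it through.** **Method.** Two-proportion normal approximation, pooled variance under the null, no continuity correction, one-sided α = 0.05 (z = 1.645), power 0.80 (z = 0.8416):

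n per arm = [1.645·√(2p̄(1−p̄)) + 0.8416·√(p₁(1−p₁)+p₂(1−p₂))]² / (p₁−p₂)²

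**Step 1: reproduce the plan.**
- Objective 1, week 3, 60% v 45%: 136 per arm (stated 136).
- Objective 1, week 6, 80% v 60%: 63.9, so 64 per arm (stated 64).
- Objective 2, 70% v 45%: 48 per group; 96/0.55 = 174.5 (stated 175).
- Objective 3, 85% v 60%: 39 per group; 78/0.45 = 173.3 (stated 174).

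All four agree, so the method is the plan's.

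**Step 2: implied week-6 group rates, taking every stratum rate as a CO rate.**
- IIa: 0.55×0.45 + 0.45×0.60 = 0.2475 + 0.27 = 0.5175.
- IIb: 0.55×0.70 + 0.45×0.85 = 0.385 + 0.3825 = 0.7675.

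**Step 3: suppose the stratum rates are right.** Expected stratum sizes are 125×0.55 = 68.75 and 125×0.45 = 56.25 per group.
- Objective 1, week 6, 80% v 51.75%: 33.8, so 34 per arm needed; power 96.5% at 64 per arm and above 99.9% at 150:125.
- Objective 2, 70% v 45% at about 69 per group: power about 91%.
- Objective 3, 85% v 60% at about 56 per group: power about 92%.

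**Step 4: suppose 60% is right for IIa and the IIb rates stay at 70% and 85%.** The extra 60 − 51.75 = 8.25 points must come from the IIa strata.

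| Where the difference goes | IIa nonresponders | IIa responders | Power, Objective 2 | Power, Objective 3 |
|---|---|---|---|---|
| All in responders: (0.60−0.2475)/0.45 | 45% | 78.3% | 91% | 23% |
| All in nonresponders: (0.60−0.27)/0.55 | 60% | 60% | 34% | 92% |
| Both strata up 8.25 points | 53.25% | 68.25% | 65% | 68% |

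Across all splits between the two extremes, the best achievable value for the weaker of the two objectives is about 66%. No split keeps both at 80%.

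**Step 5: Objective 4.**
- 80% v 67% at 125:125: p̄ = 0.735, null SE = 0.0558, alternative SE = 0.0552; (0.13 − 1.645×0.0558)/0.0552 = 0.69, so power is 75.5%. At 150:125 it is 78.9%. For 80% power, 142 per group would be needed; with 125 per group the detectable comparator is about 66%.
- 80% v the implied 76.75% (a 3.25-point difference): power 15.3% at 125:125 and 16.2% at 150:125.
- Expected precision at 150 v 125: 1.96·√(0.80×0.20/150 + 0.7675×0.2325/125) = 0.098, a 95% CI half-width of about 10 points.

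**The case against.** The strongest reply is that the average in Step 2 may mix two outcomes. Objective 3's rates are worded as keeping responder status, which Outcome Measures defines by self-reported cigarettes. On that reading no CO rate among responders is given, and 60% overall in Group IIa is compatible with a 78.3% CO response among responders. The 23% power figure would not apply either, because it would set a self-report rate against a CO rate. This stands, and it makes the finding conditional. It does not clear the text: Objective 3 would then not be sized on the CO endpoint that the section names. It would also require more Group IIa responders to have halved CO (78.3%) than to have kept their cigarette reduction (60%). That sits awkwardly with the article's own remark that people may smoke fewer cigarettes more intensively.

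A second reply is that Step 4 holds the Group IIb rates fixed while raising Group IIa, which nothing in the document requires. That is also fair. The loss of power for Objectives 2 and 3 depends on that condition.

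A reader might infer three stronger things that the document does not support:
- That the stated powers cannot all hold for Objectives 1 to 3. They can: under the stratum rates all three have at least 80%, and 60% only makes Objective 1 cautious.
- That 67% contradicts the implied 76.75% for Group IIb. It does not: 67% is offered as a detectable value for an exploratory objective, not as a forecast for Group IIb.
- That a null Objective 4 result will be reported as showing that delay does no harm. The Introduction mentions possible regulatory implications but calls the objective exploratory because of the limited follow-up. It announces no such reading.

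**Conclusion.** The point holds as a conditional inconsistency in the planning figures. If Objective 3's rates are CO rates, Group IIa's week-6 rate is 51.75% by its strata and 60% by Objective 1, a gap of 8.25 points that should be reconciled. Which rate is right matters. The stratum rates leave Objectives 1 to 3 comfortably powered. A true 60% with unchanged Group IIb rates leaves at least one of Objectives 2 and 3 at no more than about 66%. If Objective 3's rates are self-reported status, the fault is instead that its sample size departs from the stated endpoint.

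Separately, Objective 4's statement misses the plan's own 80% standard (75.5% at the stated 125 per group; 78.9% at 150:125). Under the implied Group IIb rate, the comparison would have about 15–16% power. The section does not report this, and it bears on how much the comparison can show.

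These results assume the 55/45 split, full enrolment of 150/125/125, and the uncorrected one-sided calculation that reproduces the plan's figures. The planned enrolment is not undermined. This is a correction worth making to the stated figures, not a design flaw.

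**What to change.** 1. Say which endpoint Objective 3's 85% and 60% refer to. If it is self-reported responder status, say that this calculation is not on the CO outcome, and give the assumed CO rates among responders.
2. State one set of week-6 rates in which the stratum rates average to the group rates for both IIa and IIb, and rederive the Objective 1 to 3 statements from it.
3. For Objective 4, correct either number: about 66% as the detectable comparator at 80% power with 125 per group, or 75.5% power for 80% v 67% (78.9% at 150:125). Add the expected precision, a 95% CI half-width of about 10 points at 150 v 125.

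The cost is a few sentences in the Power section. No change to enrolment or to the analysis is needed, but some stated figures will look less favourable.

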## Results

This study was approved by Advarra IRB (Pro00072765) in July 2023. Recruitment and data collection began in September 2023. Recruitment for the trial is projected to end in July 2024 and the entire study in March 2025 (with the 6-month follow-ups). We anticipate publishing study results in 2025. As of May 2024, we have enrolled 314 participants.

## Discussion

### Expected Findings

This study seeks to provide empirical evidence about the causal relationships between availability of flavored smoke-free NP products and the reduction or complete cessation of combusted cigarette smoking, a critical knowledge gap in the literature. In addition to the use of an experimental design, this study was designed to include several features intended to enhance internal and external validity. First, using a SMART design can provide multiple insights about the potential role of flavors in smoking reduction that would not be possible with traditional experimental designs (eg, randomized controlled trials). In other words, using a single study design, we will be able to assess the role of flavors in smoking reduction, maintenance of smoking reduction (among responders), potential added benefit of flavors among nonresponders (ie, the rescue), and the effect of timing (ie, immediate versus delayed access to flavors).

Second, we will remotely collect expired-air CO values. This noninvasive measure provides a validated, objective assessment of recent smoke exposure, not subject to potential bias when relying solely on self-reported cigarette consumption. This is especially relevant when blinding is not feasible as in this study [28,29].

Third, we include the unflavored or Original *on!* NP variety in the complete profile arm to assess the potentially additional effect of flavored products beyond the unflavored or Original variety. This will provide direct evidence from a counterfactual scenario whether there will be any loss of benefit from smoking reduction if a flavor ban was to be implemented for new smoke-free tobacco products, in which case only unflavored or Original products would be allowed in the market. We realize that another scenario relevant to the flavor ban is the removal of all nontobacco flavored smoke-free tobacco products from the market. In this scenario, adults who smoke cigarettes who have replaced their cigarettes with nontobacco flavored smoke-free tobacco products may relapse to smoking or choose to use tobacco-flavored or nonflavored smoke-free products instead. Our study will not provide evidence for this scenario due to considerations of resources and logistics. Future studies with a “constricting” arm where participants have access to the complete profile of smoke-free tobacco products during phase 1 and then only to tobacco-flavored or nonflavored products during phase 2 will provide direct evidence for this scenario.

Last, participants will be instructed to use the research products ad libitum in their natural environment and are allowed to use other tobacco products as they wish. This is intended to enhance external validity relative to studies that may restrict use of research or other tobacco product use or be conducted in a highly controlled laboratory environment.

### Limitations

One potential study limitation is that blinding is not feasible. Consequently, participants are aware of their group assignment. We use expired-air CO as our primary outcome to minimize potential biases in participants’ self-reported cigarette consumption. Another possible limitation is the relatively short study duration (ie, a total of 6 weeks). This study design aspect was a result of balancing feasibility and available resources while also providing sufficient time for participants to achieve a meaningful reduction in their cigarette consumption. Due to the relatively short study duration, we chose at least a 50% reduction in CO values as one of our primary outcomes—and abstinence as one of our secondary outcomes—considering we may not be able to observe the full course of smoking cessation. Previous studies using the same research products have shown measurable changes in smoking behavior in a similar timeframe [13]. Finally, this study uses a nonprobability sample, a common challenge of clinical trials. We try to mitigate these limitations by setting population quotas to align the sample with the adults who smoke cigarettes population in key demographic characteristics.

## Abbreviations

CO: carbon monoxide
CFR: Code of Federal Regulations
FDA: Food and Drug Administration
GCP: Good Clinical Practice
HPHC: harmful and potentially harmful constituent
ICF: informed consent form
IRB: institutional review board
NP: nicotine pouch
SMART: sequential, multiple assignment, randomized trial
